## Abstract

**Background:**

Proteinuria is a major marker of chronic kidney disease (CKD) progression and the predictor of cardiovascular mortality. The rapid development of renal failure is expected in those patients who have higher level of proteinuria however, some patients may have slow decline of renal function despite lower level of urinary protein excretion. The different mechanical (visco-elastic) and chemical properties, as well as the proteome profiles of urinary proteins might explain their tubular toxicity mechanism. Brillouin light scattering (BLS) and surface enhanced Raman scattering (SERS) spectroscopies are non-contact, laser optical-based techniques providing visco-elastic and chemical property information of probed human biofluids. We proposed to study and compare these properties of urinary proteins using BLS and SERS spectroscopies in nephrotic patient and validate hybrid BLS-SERS spectroscopy in diagnostic of urinary proteins as well as their profiling. The project ultimately aims for the development of an optical spectroscopic sensor for rapid, non-contact monitoring of urine samples from patients in clinical settings.

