### Participants

The 80 patients with proteinuria will be recruited form National Scientific Medical Center, admitted to the internal medicine department. Age and gender matched 20 healthy volunteers will be enrolled from the outpatient clinics. The inclusion criteria are both male and female patients with any ethnic group, aged between 18 and 65 years old and newly diagnosed patients with glomerulonephritis and different range of proteinuria. The following exclusion criteria will be used: patients aged < 18 and > 65 years, glomerular filtration rate (GFR) < 60 ml/min, pregnant females, patients with diabetes mellitus, cancer, infectious diseases, and other life-treating comorbidities/conditions. Clinical and demographics data of the participants, medical history, comorbidities and data related to the disease will be recorded in case report forms.

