### Outcome measures

The primary outcome of the study is to develop and validate the Brillouin and SERS/Raman spectroscopy for non-contact urinary protein detection and protein profiling in patients with nephrotic syndrome. The secondary outcome of the study is identifying the most hazarded protein profiles associated with adverse outcomes.

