### Statistical analysis

All statistical analyses will be performed using STATA MP Version 15 (STATA Corporation, College Station, TX) statistical package. Two-sided *P-*values less than 0.05 will be reported as a significant for all analyses. Mean ± standard deviation (SD) for normal and median - interquartile range (IQR) for abnormal distribution of numerical variables will be shown in all data. Categorical variables will be presented as numbers (percentage). Categorical variables will be compared using Chi-square test or Fisher’s exact test and continuous variables will be compared using Kruskal–Wallis and/or Mann–Whitney U-test, as appropriate. Comparison of repeated two or more variables will be assessed with Wilcoxon and/or Friedman test as appropriate.

Obtained measurements of urinary protein by Brillouin and SERS/Raman spectroscopy will be compared with LC-MS data from same participant urine samples. Correlation between Brillouin and SERS/Raman spectroscopy parameters, LC-MS data and clinical-laboratory data of patients as well as healthy participants will be provided using Pearson’s or Spearman’s correlation as appropriate.

Univariate logistic regression will be used to test the association of several risk factors with high level of proteinuria. Multivariate logistic regression analysis will be used to assess the predictors for adverse outcomes. A receiver operator characteristics curve (ROC curve) analysis will be performed to identify the sensitivity, specificity, negative and positive predictive values of cut-off levels of Brillouin and SERS/Raman spectroscopy parameters in prediction of high proteinuria. Between measurement comparison of AUC will be provided with method developed by DeLong et al. [25].

During 1 year of follow-up, all adverse events such as exacerbation of proteinuria, progression of CKD, complications of nephrotic syndrome (thrombosis, nephrotic crisis, infection, including death), disease relapse rate and inefficacy of treatment regimen will be registered with referencing incident dates. Unadjusted and adjusted regression models will be evaluated to identify the association between urinary protein profiles defined by Brillouin and SERS/Raman spectroscopy and abovementioned adverse outcomes.

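### Cut-offs for high proteinuria are found and judged on the same samples, so sensitivity, specificity, PPV and NPV will be moderately overstated; AUCs are affected only if parameters are selected or combined

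*Protocol article*

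**What the plan says.** All references are to the protocol article.

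- **Outcome measures:** "The primary outcome of the study is to develop and validate the Brillouin and SERS/Raman spectroscopy for non-contact urinary protein detection".
- **Participants:** one cohort. "The 80 patients with proteinuria will be recruited form National Scientific Medical Center", and "Age and gender matched 20 healthy volunteers will be enrolled from the outpatient clinics". No second cohort or hold-out set is described.
- **Statistical analysis, accuracy:** ROC analysis is used "to identify the sensitivity, specificity, negative and positive predictive values of cut-off levels of Brillouin and SERS/Raman spectroscopy parameters in prediction of high proteinuria". The parameters are plural and unnamed, and neither a cut-off nor a rule for choosing one is given.
- **Statistical analysis, AUCs:** "Between measurement comparison of AUC will be provided with method developed by DeLong" and co-workers.
- **Statistical analysis, significance:** two-sided P-values: "values less than 0.05 will be reported as a significant for all analyses".
- **Discussion, opening:** the authors know of no earlier study that diagnosed proteinuria from urine with these spectroscopies.

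**The concern.** A cut-off chosen because it separates these samples well also fits their chance features. Sensitivity, specificity, PPV and NPV read off at that cut-off in the same samples are then too favourable on average. The article describes no step that would correct this, and it offers no outside source for a cut-off.

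Two kinds of validation that the article does mention do not fill the gap. The comparison with LC-MS uses the same participants' urine and tests agreement between methods. The measurement-validation stage under Study design comes before recruitment. Neither tests a cut-off in patients other than those who produced it.

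At stake is how far the reported accuracy would hold in new patients. The article looks ahead to clinical deployment of the sensor, so optimistic cut-offs could be carried forward.

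**Working it through.** **No figure to reproduce.** The article states no target AUC, precision or accuracy, so the size of the bias was estimated by simulation.

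**Inputs from the article:** 80 patients, 20 volunteers, two-sided 0.05.

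**Assumptions, because the article does not give them:**
- normally distributed markers with equal spread;
- the cut-off maximises J = sensitivity + specificity − 1 (Youden);
- high versus not-high splits of 40/40 and 20/60 (80 patients), and 40/60 and 80/20 (all 100).

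**Step 1. True values for one real marker.** With AUC = Φ(d/√2), d = √2·Φ⁻¹(AUC), and the best attainable J is 2Φ(d/2) − 1.
- AUC 0.70: d = 0.742, best J = 0.289.
- AUC 0.90: d = 1.812, best J = 0.635.

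**Step 2. Apparent J at AUC 0.70,** with the cut-off chosen and judged on the same samples (1,500 replicates per split):

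| Split | Apparent J | True J at the chosen cut-off | Overstatement |
|---|---|---|---|
| 40/40 | 0.377 | 0.266 | 0.111 |
| 20/60 | 0.385 | 0.261 | 0.124 |
| 40/60 | 0.365 | 0.269 | 0.096 |
| 80/20 | 0.386 | 0.265 | 0.121 |

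Against the cut-off actually chosen, the overstatement is 0.10 to 0.12. Against the best attainable J it is smaller: 0.365 − 0.289 = 0.076 up to 0.386 − 0.289 = 0.097. Taking both yardsticks gives about 0.08 to 0.12.

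**Step 3. The same at AUC 0.90.** Apparent J is about 0.69 to 0.71. Against the best attainable value the excess is 0.69 − 0.635 = 0.055 up to 0.71 − 0.635 = 0.075. Against the chosen cut-off it is 0.075 to 0.09. Together this is about 0.06 to 0.09.

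**Step 4. AUC of one parameter fixed in advance, direction included.** Mean estimated AUC was 0.498 to 0.503 when the truth is 0.50, and 0.699 to 0.703 when it is 0.70. There is no bias, because no cut-off enters.

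**Step 5. AUC when the best of several is picked.** Independent parameters with no signal (true AUC 0.50):

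| Split | Best of 5 | Best of 20 |
|---|---|---|
| 40/40 | 0.603 | 0.640 |
| 20/60 | 0.619 | 0.662 |
| 40/60 | 0.593 | 0.627 |
| 80/20 | 0.614 | 0.658 |

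For the two splits of the 80 patients, this is 0.60 to 0.62 for the best of 5 and 0.64 to 0.66 for the best of 20. The chance that at least one parameter reaches P < 0.05 is 1 − 0.95⁵ = 22.6% for 5 and 1 − 0.95²⁰ = 64.2% for 20. The counts 5 and 20 are illustrations. Correlated parameters give less: at 40/40 with correlation 0.8, best of 20 falls from 0.64 to 0.60.

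**The case against.** **The article is silent rather than opposed.** No fuller protocol or analysis plan is shown, and resampling mechanics are often left to such documents. That is fair, and an unseen plan may contain the correction. The point still stands on what is written: the article does state the accuracy method, in one cohort, with no outside cut-off available.

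**A reader might infer that all the AUCs, and the DeLong comparison with them, are inflated.** The documents do not support this. Step 4 shows no bias for a parameter fixed in advance, and DeLong's method is valid for measured markers that were not selected on the same data. The article does not say that the best parameter will be picked.

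**A reader might infer that a fitted hybrid score will be the most inflated result.** The abstract does aim to "validate hybrid BLS-SERS spectroscopy in diagnostic of urinary proteins as well as their profiling", but the section on the hybrid system describes an instrument that makes two measurements with one laser source. Statistical analysis plans no ROC analysis of a fitted combination, so inflation figures for such a score would describe a model the article does not propose.

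**A reader might infer that the validation claim in the primary outcome collapses.** That goes too far. Much of it rests on comparison and correlation with LC-MS, and the ROC analysis answers the narrower question of predicting high proteinuria. What is unsupported is treating the cut-offs themselves as validated.

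**The bias is modest.** Spread over two quantities, it is roughly 0.04 to 0.06 each for sensitivity and specificity, in a study that calls itself the first in its field. The Discussion also gives a physical reason why Brillouin measures should follow protein concentration, so zero signal is an extreme case. This stands and lowers the severity.

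**Conclusion.** The point holds in a limited form. Following the article as written gives optimistic sensitivity, specificity, PPV and NPV, even with a single real parameter. Sensitivity plus specificity is overstated by about 0.08 to 0.12 at AUC 0.70 and about 0.06 to 0.09 at AUC 0.90. These sizes rest on normal markers, a Youden-type cut-off and the assumed splits. PPV and NPV share the problem, but their bias was not quantified.

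Inflation of AUCs and of DeLong comparisons is conditional: it arises only if parameters are selected or combined on the same data. Its size depends on a parameter count that the article does not give.

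The severity is moderate. Nothing in design, recruitment or data collection has to change, and the correction can be made on the finished dataset.

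**What to change.** In Statistical analysis:

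1. Name the Brillouin and SERS/Raman parameters and the rule for choosing each cut-off before the data are analysed.
2. Report sensitivity, specificity, PPV and NPV corrected by bootstrap optimism correction or repeated cross-validation, beside the apparent values. Repeat the cut-off choice, and any selection or combination of parameters, inside every resample.
3. Keep DeLong's method for single parameters specified in advance. For any selected or combined score, compare out-of-fold predictions with bootstrap confidence intervals.
4. Describe the cut-offs as development results until they have been tested in independent samples.

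The cost is some extra analysis work and slightly less favourable accuracy figures. No new patients or measurements are needed.

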To date, different diagnostic methods in clinical settings can be used to ascertain urinary proteins. The extent of proteinuria can be gauged using an albumin-specific dipstick, immunochemical techniques, and high-performance liquid chromatography [12, 13]. However, results may vary between the methods, possibly due to different type, origin and size of excreting urinary proteins. The quality and quantity of filtered proteins, especially their mechanical properties such as physical viscosity [14, 15] compressibility [16] and chemical properties [17], such as amino-acid sequence (type of peptides), and molecular weight (low, middle and high molecular weight proteins), identify what kind of urinary proteins are more toxic and hazardous [1, 17]. Further studies including different areas of biomedicine and biophysics are needed to better understand importance of mechano-chemical characteristics of urinary proteins, in providing diagnostic and prognostic information that influences patient care and outcomes.

Measuring the viscosity, elasticity and chemistry of biological fluids is an important analytical tool in diagnostic, prognostic, and preventive medicine and research [14, 15]. The viscosity of biological solvents helps in gaining insight into the kinetics and dynamics of molecular and cellular processes such as conformational changes in protein [18, 19]. Such optical techniques as Brillouin and Raman spectroscopies to analyze human biofluids are very attractive for potential non-contact and fast clinical diagnostics with minimal or no sample preparation, without alteration of the fluid obtained from the body, representing a powerful simplification over most current techniques. Recently, dual Brillouin-Raman spectroscopy has been demonstrated as a viable diagnostic sensing tool in variety of biomedical applications [20–23].

The goal of the project is to develop and validate combined Brillouin & Surface-Enhanced Raman Scattering (SERS) Spectroscopy technique for simultaneous non-contact assessment of visco-elastic and chemical properties of human urine proteins as biomarkers of kidney disease. Systematic studies of these properties in proteins of urine samples to be taken from diseased and healthy subjects will be cross-validated by Liquid Chromatography Mass Spectrometry (LC-MS). The project ultimately aims for development of optical spectroscopic sensor for rapid, non-contact monitoring of urine samples from patients in clinical setting.

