### Hybrid Brillouin-SERS system

We propose to construct hybrid Brillouin-Raman system, which will simultaneously assess both visco-elastic (i.e. mechanical) and chemical properties at the same time from the same excitation laser source (532 nm or 780 nm). In this arrangement our Brillouin hyperfine spectrometer (Light Machinnery, Canada) system will be coupled with confocal microscope (Nicon, Japan) and Nanofinder Raman spectrometer (SOL Instruments, Belarus) and motorized sample stage (Standa, Lithuania) for 3D imaging The schematic of the proposed hybrid all-optical system is displayed in the Fig. 4.

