Summarizing the available relevant literature and emphasizing the scientific novelty and significance of dual Brillouin-SERS spectroscopy, we will try to study and cover following question in this proposed project: Do non-contact dual Brillouin-SERS spectroscopy provide differential and diagnostic information on mechano-chemical profile of urine and urinary protein in healthy subjects and patients with different range of proteinuria?

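### The combined Brillouin–SERS technique is what the study sets out to validate, but the named diagnostic analyses work on individual parameters and define no joint index

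*Protocol article*

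**What the plan says.** **The aim is the combination.** The Abstract (Background) proposes to "validate hybrid BLS-SERS spectroscopy in diagnostic of urinary proteins as well as their profiling". The Background section sets the goal as to "develop and validate combined Brillouin & Surface-Enhanced Raman Scattering (SERS) Spectroscopy technique for simultaneous non-contact assessment". The study question in the Discussion is: "Do non-contact dual Brillouin-SERS spectroscopy provide differential and diagnostic information on mechano-chemical profile of urine and urinary protein". The section on the hybrid system describes one instrument that will "simultaneously assess both visco-elastic (i.e. mechanical) and chemical properties at the same time from the same excitation laser source". The list of expected results after the Discussion includes building that instrument, cross-validating it against LC-MS and planning its move to the clinic.

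**The primary outcome is worded more loosely.** Under Outcome measures it is to "develop and validate the Brillouin and SERS/Raman spectroscopy for non-contact urinary protein detection and protein profiling", with no mention of a hybrid or combined reading.

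**The analysis names these diagnostic steps** (Methods, Statistical analysis):
- comparison of the spectroscopy measurements with LC-MS in the same samples, and Pearson or Spearman correlations;
- univariate logistic regression for high proteinuria;
- ROC analysis for "cut-off levels of Brillouin and SERS/Raman spectroscopy parameters in prediction of high proteinuria";
- a DeLong comparison of AUCs between measurements.

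Multivariate logistic regression is named for adverse outcomes. A final paragraph adds unadjusted and adjusted models that relate protein profiles from the two spectroscopies to those same outcomes.

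**The concern.** Validating a combined test calls for an analysis of the combined result. That means one index that uses both signals, its accuracy against the target, and preferably its accuracy beside each signal alone. No diagnostic step named in the article defines such an index. A cut-off applies to one scalar, and no scalar built from both readings is described. The one regression named for high proteinuria, which is also the ROC target, is univariate.

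Followed as written, the plan can report how well each parameter discriminates and which has the larger AUC. It need not produce an accuracy figure for the combined reading, and it cannot distinguish two complementary signals from two that largely repeat each other. The Discussion makes redundancy plausible. It presents Brillouin scattering as a possible measure of total protein concentration, and SERS as a way to strengthen a Raman signal that is otherwise too weak to detect urinary albumin well.

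**Working it through.** **Aim against analysis.** The article states no AUC, power or sample-size derivation, so there is no figure of its own to reproduce. The first check sets the texts side by side.

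| Named step | Works on | Joint Brillouin–SERS index? |
|---|---|---|
| Correlation | pairs of variables | none named |
| ROC cut-offs | spectroscopy parameters | none named |
| DeLong | AUCs of different measurements | none named |
| Logistic regression, high proteinuria | one factor at a time | excluded by univariate |
| Logistic regression, adverse outcomes | several predictors | possible, but serves the secondary outcome |

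**Do separate AUCs determine the combined AUC?** This is an illustration. The AUCs and correlations below are assumptions, because the article gives none.

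Under an equal-variance binormal model, a marker with area AUC separates the groups by d = √2 · Φ⁻¹(AUC). For two markers with within-group correlation ρ, the best linear score has

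D² = (d₁² − 2ρd₁d₂ + d₂²)/(1 − ρ²), and AUC = Φ(D/√2).

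With both AUCs at 0.75, Φ⁻¹(0.75) = 0.6745, so d = 0.954 and d² = 0.910. For equal markers the formula reduces to D² = 2d²/(1 + ρ) = 1.820/(1 + ρ).

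| ρ | D² | D/√2 | Combined AUC | Gain over 0.75 |
|---|---|---|---|---|
| 0 | 1.820 | 0.954 | 0.830 | 0.080 |
| 0.3 | 1.400 | 0.837 | 0.799 | 0.049 |
| 0.6 | 1.137 | 0.754 | 0.775 | 0.025 |
| 0.8 | 1.011 | 0.711 | 0.761 | 0.011 |

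The two single AUCs are the same in every row, so a comparison of one with the other has an expected difference of 0 throughout, while the gain runs from 0.011 to 0.080. The zero follows from choosing equal AUCs. With 0.80 and 0.70 the expected difference is 0.10 whatever ρ is, and the combined AUC is 0.839, 0.813, 0.800 or 0.810 at ρ = 0, 0.3, 0.6 or 0.8. In both cases the single AUCs alone do not fix the combined one.

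**Precision available.** The Participants section gives 80 patients and 20 healthy volunteers. How many count as having high proteinuria is not given, so several splits were tried. Hanley–McNeil 95% half-widths for one AUC are:

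| High / not high | AUC 0.75 | AUC 0.80 |
|---|---|---|
| 80 / 20 | 0.106 | 0.093 |
| 40 / 40 | 0.107 | 0.098 |
| 40 / 60 | 0.101 | 0.093 |
| 20 / 60 | 0.134 | 0.125 |

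Simulated power (2,000 runs, two-sided 0.05) of a DeLong test of the combined score against one of two AUC-0.75 markers was 46%, 26% and 12% at ρ = 0, 0.3 and 0.6 with a 40/40 split. With 80/20 it was 39%, 23% and 11%. The score weights were treated as known, so these figures leave out the cost of estimating them.

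**The case against.** The strongest reply is that this is a condensed article and the argument rests partly on silence.

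- **Ambiguous wording.** The ROC sentence does not say that the modalities are analysed only separately, and the DeLong sentence does not list the measurements compared. This stands. It rules out the claim that a combined score is never used. Still, cut-offs and a between-measurement comparison read most naturally as separate parameters, and the only model named for high proteinuria is univariate.
- **Other joint uses.** The profiles in the adverse-outcome models may draw on both modalities, and the LC-MS section plans to assess molecular-weight fractions on the hybrid system. Both stand. The first serves the secondary outcome. The second is described as comparative characterisation and correlation, with no diagnostic accuracy measure.
- **The study question.** A reader might infer that the question goes unanswered. The article does not support that. The question asks whether the dual technique gives differential and diagnostic information in healthy subjects and patients. Group comparisons, comparison with LC-MS and single-parameter ROC analyses address this in part. The primary outcome and the analysis also use similar wording.
- **Superiority as the aim.** A reader might also infer that the hybrid exists to beat either modality. No section says so. The stated reason is simultaneous assessment of mechanical and chemical properties. Added value is a useful quantity to report, but it is not a declared objective.
- **Score and instrument differ.** Stand-alone Brillouin uses 532 nm and SERS 785 nm, while the hybrid uses one common source (532 or 780 nm). A score built from stand-alone readings does not by itself validate the hybrid instrument. This stands as a limit on the remedy.

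**Conclusion.** The point holds as a gap between a declared aim and the diagnostic analyses named to serve it. The combined technique is to be validated, yet no named diagnostic analysis yields the accuracy of a combined reading or its difference from each modality alone. It does not hold as a claim that the two readings are nowhere combined or that the study fails to answer its question.

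The size of what is left open cannot be read from the article. On assumed single AUCs of 0.75 under a binormal model, the combined AUC lies about 0.01 to 0.08 above either modality, depending on a correlation that is not given. The gain would be poorly estimated at this sample size. That is a reason to report it with an interval rather than to leave it out. The change is worth making because it is cheap and matches the stated goal, but the existing analyses are not invalid without it.

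**What to change.** In Statistical analysis, add one pre-specified joint score for high proteinuria: a logistic model on one or a few Brillouin and SERS parameters, chosen in advance and measured on the same samples. State whether the readings come from the hybrid system or from the stand-alone instruments. Then report:

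1. the cross-validated AUC of the joint score with a 95% confidence interval;
2. its difference from a Brillouin-only and a SERS-only model, each built and cross-validated in the same way, with intervals. The method should allow for nested models fitted on the same data, for example by repeating the whole fit and cross-validation within a bootstrap. A plain DeLong test on in-sample fits is not suitable.

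**Cost.** A little more analysis and no new samples or measurements if the readings are collected as planned. The number of parameters has to stay small, and cross-validation is needed because the weights are estimated in the same participants. With 80 patients and 20 controls the interval around the gain will be wide, so it should be described as an estimate and not as a powered test of superiority.
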